# Improving uptake of pediatric vaccines through religious conferences and mobile vaccine clinics in Aceh, Indonesia (TABRIE): study protocol for a stepped wedge cluster randomized controlled trial

**DOI:** 10.1186/s13063-025-09170-5

**Published:** 2025-11-21

**Keywords:** Routine pediatric vaccination, Vaccine hesitancy, Public health intervention, Mobile vaccine clinics, Religious leader conferences, Community health workers, Religious leaders, Stepped wedge cluster randomized controlled trial, Low- and middle-income countries, Indonesia

## Abstract

**Background:**

Despite advancements in child immunization, inadequate immunization rates in low- and middle-income countries persist due to inadequate health infrastructure, challenges in vaccine supply and distribution, insufficient healthcare provider training, and low levels of community trust in vaccines. Aceh, a religiously conservative province in Indonesia, has low pediatric vaccination coverage and exemplifies the need for innovative vaccine delivery models. Evidence suggests interventions should target both logistical barriers (e.g., distance or clinic wait times) and societal factors, including misinformation, that contribute towards vaccine hesitancy.

**Methods:**

The trial “TABRIE” will measure the impact of two strategies on children’s vaccination rates and parental attitudes towards vaccines in Banda Aceh and Aceh Besar, Indonesia, compared to current outreach strategies. The two strategies being tested are (a) an informational conference with religious leaders who work in specific clinics and (b) a mobile vaccine clinic staffed with community health workers conducting a variety of outreach events. We will execute a stepped wedge cluster randomized design with baseline measures and a cross-sectional sampling structure. Twelve districts (*Kecamatan*) will be randomized into one of the two strategies. In year 1, three districts from each strategy will implement the intervention, with the other three districts implementing the strategy in the second year. We will conduct cross-sectional surveys in September 2023 (baseline), September 2024 (year 1), and September 2025 (year 2). The primary outcome is the proportion of fully vaccinated children aged 1–5 years for bacillus Calmette-Guérin (BCG), diphtheria-tetanus-pertussis (DTP), polio, and measles. Secondary outcomes include the proportion of children aged 1–5 years with at least one dose of DTP and measles vaccines, the proportion of vaccine-hesitant parents, social norms surrounding vaccination, parental trust in community health workers to administer vaccines, the proportion of parents experiencing distance barriers to vaccination, the proportion of parents reporting that their religious leader encourages vaccination, and the proportion of parents receiving vaccination information from their religious leader.

**Discussion:**

This study will conduct a stepped wedge cluster randomized trial to separately estimate the effects of religious conferences and mobile vaccine clinics on pediatric vaccination rates and parental attitudes towards vaccination. It will offer a novel paradigm in vaccination delivery by inserting vaccination from clinics into social spaces that provide alternative, community-centered policy solutions to vaccine hesitancy.

**Trial registration:**

ClinicalTrials.gov NCT06160999. Registered on December 14, 2023.

## Introduction

### Background and rationale {6a}

Despite significant advances in global childhood vaccination, immunization rates in many parts of the world remain insufficient. Vaccine disparities are particularly evident in low- and middle-income countries (LMICs), where coverage against diphtheria, pertussis, and tetanus—a key indicator of access to routine vaccination services—falls below 50% in many regions [1]. Coverage gaps have been further widened by the COVID-19 pandemic [2]. Barriers to vaccine distribution and utilization in LMICs include inadequate health facilities and local public health infrastructure, unreliable vaccine supply, storage, and transport capabilities, and lack of health care provider and/or proxy availability and training [3]. Behavioral and social drivers of vaccination are similarly important and include perceived disease risk, vaccine confidence, and social norms [4].

Although public approval of childhood vaccines is generally high in LMICs, there may be regional variations in acceptance and uptake that reveal inequities in vaccine access and/or confidence. According to the SAGE (Strategic Advisory Group of Experts on Immunization) Working Group on Vaccine Hesitancy, this lack of confidence may be manifested as vaccine hesitancy, defined as delay in acceptance or refusal of vaccines despite the availability of vaccination services [5]. Vaccine hesitancy is complex and content-specific and may be attributable to low levels of trust in vaccines and/or delivery systems; low perceived risk of vaccine-preventable disease; or barriers to accessibility, affordability, and availability, among other issues [6]. While health workers remain trusted sources of vaccine information and key influencers in immunization decision-making, they may face significant time constraints and resource limitations that impair their ability to administer vaccines and/or provide needed counseling. A major challenge, therefore, is the shortage of individuals who are culturally competent and equipped to administer vaccines and provide counseling. Ensuring that these individuals are well-trained and closely connected to the local communities they serve is critical.

Our study seeks to create a paradigm shift in how the public views and utilizes vaccination services. Currently, community health centers remain the default setting for vaccination, and clinicians the default administrators. However, the general population may have difficulty accessing these clinics or trusting traditional vaccination providers, particularly if they are members of marginalized communities that have experienced medical discrimination. Our study applies a two-pronged approach to address issues of trust and ease of access among the general population by (a) mobilizing religious communities to discuss vaccines (to counter reported lack of information about vaccines among unvaccinated families) and (b) training more community health workers in vaccination and in physically delivering vaccines through a mobile vaccine clinic (MVC) concept to facilitate ease in accessing vaccines. By mobilizing these individuals in the community settings where people live, work, worship, and learn, we aim to expand vaccine information and services. Through community engagement, we believe we can promote a participatory process in multiple aspects of the immunization program, a process that has been piloted in domestic settings [7].

More specifically, we plan to work with local health leaders in a low vaccination community in Aceh, Indonesia, to identify social institutions that are part of children and families’ daily lives; these could include houses of worship, schools, or community centers. We will fund a mobile vaccine delivery unit to go to these locations to physically bring vaccines to the people and to link them with existing immunization clinic infrastructure. We will also work towards changing the culture of child health and vaccination through substantial discussions and conversations with multiple levels of religious leaders at conferences. Overall, we hope to develop a simple and scalable training and recruitment program to equip community health workers to administer vaccines and religious leaders to provide culturally appropriate and specific counseling—all within familiar, comfortable social spaces. More than a one-time vaccination campaign, we hope to create a sustainable proxy network that can be deployed repeatedly, at intervals consistent with recommended vaccine schedules.

Case studies provide support for this approach. For example, a Pakistan provincial government deployed 13,000 women-led vaccination teams to local communities to provide COVID-19 immunization counseling, administration, and data entry [8]. In addition to traveling to people’s homes, these workers also offered vaccines in local temples, communal squares, and other public spaces. Another example would be the distribution of hepatitis B vaccines by trained community leaders at gay pride events [9]. MVCs have been positively viewed in a variety of settings—including COVID-19 clinics in Boston, universities in the USA, and in emergency settings in places like Afghanistan, Haiti, and Palestine [10–12]. However, there is limited information about their routine use in LMIC settings. Our study builds on these previous models by inserting vaccination into diverse social spaces, simultaneously “liberating” vaccine administration from clinics and increasing convenient access to vaccines. Our model has the potential to reach children and families that are currently excluded from receiving vaccines or information from more formal, clinic-based vaccination services.

This protocol describes the TABRIE study which aims to evaluate the impact of two vaccine uptake strategies on children vaccination rates and parental attitudes towards vaccines in Banda Aceh and Aceh Besar, two study locations in the province of Aceh, Indonesia.

### Objectives {7}

The primary objective of the study is to examine the impact of the two interventions—MVC and religious conferences—on full vaccination coverage at the district level. The secondary objective is to examine the effect of these interventions on uptakes of specific vaccines, measures of vaccine hesitancy, and other barriers to vaccination uptake. While the study is not powered for a direct head-to-head comparison between MVC and religious conferences, we will perform exploratory analyses comparing the two interventions and interpret the results cautiously. Primary objective measure will be the proportion of children 1–5 years of age fully vaccinated (receipt of bacillus Calmette-Guérin, diphtheria-tetanus-pertussis, polio, and measles vaccines).

Hypothesis for primary objective: We expect that the intervention arms will have greater vaccination coverage than the non-intervention arms.

Secondary objective measures: (a) proportion of children 1–5 years of age with one dose of diphtheria-tetanus-pertussis vaccine; (b) proportion of children 1–5 years of age with a measles vaccine; (c) proportion of parents vaccine hesitant; (d) proportion of parents stating a social norm towards vaccination; (e) proportion of parents with trust in a community health worker to administer vaccines; (f) proportion of parents stating that distance is a barrier to vaccination; (g) proportion of parents stating that their religious leader wants them to be vaccinated; and (h) proportion of parents receiving vaccination information from their religious leader.

Hypothesis for secondary objective: Our secondary objectives are exploratory and we do not present pre-existing hypotheses.

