### Trial design {8}

The 2-year study is conducted in a stepped wedge cluster randomized design [13]. Our clustered unit of analysis is a district, or *Kecamatan*, in Indonesia. Because we have two interventions, we are running two concurrent trials. Each intervention will involve 6 districts, for 12 districts involved total. Each district typically has one or two *Puskesmas* (*Pusat Kesehatan Masyarakat*) or community health clinics—the location of most vaccinations. Each district also is composed of several villages.

Our study location is Banda Aceh, the provincial capital of Aceh, and Aceh Besar, the surrounding suburban area. There are a total of 41 districts in Banda Aceh and Aceh Besar. We randomly sampled 18 of these. We subsequently performed a cluster analysis, where we clustered these 18 districts into 2 groups based on the following district-level characteristics: (a) population density; (b) *Puskesmas* building conditions—variables indicating the condition of *Puskesmas* buildings, such as good, lightly damaged, moderately damaged, and heavily damaged; (c) healthcare personnel—number of general practitioners, midwives, and community health workers in each district; (d) auxiliary *Puskesmas* conditions including good, lightly damaged, moderately damaged, and heavily damaged; (e) educational institutions—number of *Poskestren* (Islamic boarding schools); (f) healthcare facilities—number of beds and maternity care beds available; and (g) internet network availability—status of internet networks, including good, not smooth, and none.

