The first group had 12 districts, and the second six districts. For the first 12 districts, we additionally removed six districts whose population center was close to the population center of another district to avoid spillovers. In this way, we ended with six districts in each group. We then randomly assigned the two groups to either the MVC strategy or the religious conference strategy. Thus, the six districts from the first group were assigned to the MVC strategy, and the six districts in the second group were assigned to the religious conference strategy (Table 1). For each group of 6, 3 districts were from Banda Aceh, and 3 from Aceh Besar. Within each group, we then randomized three districts to begin the intervention in year 1 and three in year 2 using a computer-generated allocation. District authorities were informed only after randomization. Although the strategies were implemented simultaneously, analytically, these are treated as two separate trials. The stepped wedge design and the district schedule for the two interventions are depicted in Fig. 1 and Table 1.

**Table 1 Tab1:** Sites of the two interventions, TABRIE, Aceh, Indonesia, 2023–2025

Strategy	Year(s) of intervention (randomized)	Location	District
Mobile vaccine clinic (MVC)	1 and 2	Banda Aceh	Baiturrahman
MVC	1 and 2	Banda Aceh	Jaya Baru
MVC	1 and 2	Aceh Besar	Mesjid Raya
MVC	2	Banda Aceh	Kuta Raja
MVC	2	Aceh Besar	Peukan Bada
MVC	2	Aceh Besar	Krueng Barona Jaya
Religious conference	1 and 2	Aceh Besar	Kuta Malaka
Religious conference	1 and 2	Aceh Besar	Darussalam
Religious conference	1 and 2	Banda Aceh	Meuraxa
Religious conference	2	Banda Aceh	Kuta Alam
Religious conference	2	Banda Aceh	Lueng Bata
Religious conference	2	Aceh Besar	Montasik

Year of intervention start was randomized within each intervention arm (3 districts began in year 1 and 3 in year 2)

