### Sample size {14}

For this cluster randomized control trial, we specified a stepped wedge design with baseline measures and a cross-sectional sampling structure. The primary outcome is the net difference between arms in repeated cross-sectional samples. We used the following parameters for sample size calculation: (a) type I error rate: 0.05; (b) power: 0.80; (c) expected vaccination proportion in controls: 49.5% (based on the 2022 survey); and (d) intraclass correlation coefficient (ICC): 0.0816 (based on the 2022 survey).

To detect a 13 percentage point increase in vaccination coverage (62.5% in the intervention arm vs. 49.5% in the control arm), we determined that 100 individuals per cluster are required. With a stepped wedge design involving three clusters in the first year and three in the second year, this sample size provides adequate power to detect the specified effect size. The sample size calculation assumed an exchangeable (time-invariant) intracluster correlation; no temporal decay was assumed.

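### Strategy was assigned by one draw between two cluster-analysis groups, not by district, so the exploratory MVC-versus-conference comparison is aliased with district group as well as underpowered

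*Protocol article*

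**What the plan says.** The protocol article describes the allocation of strategy in two ways.

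- **Abstract, Methods:** the twelve districts "will be randomized into one of the two strategies".
- **Trial design {8}:** 18 districts were sampled, and "we clustered these 18 districts into 2 groups based on the following district-level characteristics". The characteristics listed are population density, condition of main and auxiliary clinic buildings, health personnel, Islamic boarding schools, beds, and internet availability. The groups had 12 and 6 districts. Six districts were removed from the larger group because their population centres lay close to another district's; no such step is described for the smaller group. Then: "We then randomly assigned the two groups to either the MVC strategy or the religious conference strategy". Within each group of six, start year was randomised, three districts to year 1 and three to year 2. Each group has three Banda Aceh and three Aceh Besar districts, and the strategies are analysed as two separate trials.

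Objectives {7} says that the study is not powered for a head-to-head comparison, but that "we will perform exploratory analyses comparing the two interventions and interpret the results cautiously". It gives no other limitation. The covariates in Statistical methods {20a} are respondent and child characteristics; no district characteristic is among them.

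**The concern.** The abstract gives the wrong unit of randomisation for strategy. A reader who relies on it would take MVC versus conference to be a randomised comparison of six districts with six, short only of sample size. In fact whole groups were allocated, and they came from a procedure that puts similar districts together, so the groups are expected to differ on at least some of its inputs. Some of those inputs could plausibly change how well these strategies work: numbers of community health workers for a clinic that they staff, boarding schools for an approach through religious leaders, density for access.

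If the two strategies appear to differ, the cause could be the strategy or the kind of district that received it. A caution about power implies that more data would settle the matter. It would not.

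**Working it through.** **1. What was randomised, and how many ways it could have fallen**

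| Comparison | Randomised unit | Possible allocations |
|---|---|---|
| MVC vs conference, as done | group of six districts (2 units) | 2 |
| MVC vs conference, as the abstract reads (6:6) | district (12 units) | C(12,6) = 924 |
| The same, stratified 3:3 by location | district | C(6,3)² = 400 |
| Start year within one strategy | district (6 units) | C(6,3) = 20 |

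With 2 equally likely allocations, a randomisation test of strategy cannot give p below 1/2 = 0.5 one-sided or 1.0 two-sided, however many children are surveyed. There is no second group within either strategy, so a term for group cannot be fitted beside a term for strategy.

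**2. The plan's own sample size, reproduced**

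Inputs from Sample size {14}: alpha 0.05 (two-sided assumed), power 0.80, 49.5% vs 62.5%, ICC 0.0816 with no decay, 100 per cluster (read as per survey), 3 + 3 clusters. The Hussey–Hughes variance is used with I = 6 clusters, T = 3 periods and sequences 0-1-1 and 0-0-1:

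- U = 9 (treated cluster-periods), W = 0² + 3² + 6² = 45, V = 3×2² + 3×1² = 15
- IU − W = 9; U² + ITU − TW − IV = 81 + 162 − 135 − 90 = 18
- Total variance at the mean proportion: 0.56 × 0.44 = 0.2464
- τ² = 0.0816 × 0.2464 = 0.02011; s = 0.9184 × 0.2464 / 100 = 0.002263
- Var = 6s(s + 3τ²) / (9s + 18τ²) = 0.002223, so SE = 0.0471
- Power = Φ(0.13/0.0471 − 1.96) = 0.787

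Other choices of the proportion give 0.782 to 0.794, close to the stated 0.80. That calculation concerns intervention against control, not one strategy against the other.

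**3. The power limitation that the plan states**

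For the difference between two such independent effects:

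- SE = 0.0471 × √2 = 0.0667
- Detectable difference at 80% power: 2.80 × 0.0667 = 18.7 points
- Power for a 13-point difference: Φ(0.13/0.0667 − 1.96) = 0.50

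The stated limitation is true.

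**4. The limitation that it does not state**

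Assume that the strategies are equally effective, but that effects differ between the two groups by δ for district reasons. The values of δ are assumptions; the protocol gives none. The rejection rate of a nominal 5% test is Φ(δ/SE − 1.96) + Φ(−δ/SE − 1.96). The 400 row is a hypothetical larger survey: s = 0.000566, single-effect SE = 0.0237, difference SE = 0.0336.

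| Children per district per survey | δ = 0 | δ = 5 points | δ = 10 points | δ = 13 points |
|---|---|---|---|---|
| 100 | 5% | 12% | 32% | 50% |
| 400 | 5% | 32% | 85% | 97% |

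A larger sample shrinks the standard error and leaves δ in place, so a false attribution to strategy becomes more likely.

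**5. Levels and effects**

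The primary model estimates each effect with period effects and a cluster intercept, and start year is randomised within group. If the head-to-head compares the two within-group effects, stable differences in coverage between groups largely cancel. Different responses to intervention and different time trends do not. A comparison of raw coverage would carry the level differences as well. The protocol does not say which comparison is meant.

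**The case against.** The strongest defence is that the design section discloses the whole procedure, calls the strategies two trials analysed separately, labels the comparison exploratory and promises caution. The power limitation is correct, no randomisation test is planned, and location is balanced 3:3. This stands, and it limits the severity. It does not supply the missing reason for caution, and it leaves the abstract contradicting the design section. The count of 2 allocations is not an error in a planned test; it shows that group is not replicated within strategy.

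A reader might infer more than the documents support:

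- **That the groups were made to differ on purpose.** No such aim is stated. Difference is only what a cluster analysis would be expected to produce.
- **That confounding is complete on every listed characteristic.** Aliasing is exact for the group label. On any single characteristic the groups may overlap, and after trimming the remaining differences are not reported.
- **That the trial's main results are compromised.** Each strategy's effect against control rests on the start year randomised within its own group.
- **That no interval may be shown for the difference.** An interval clearly labelled as non-randomised is acceptable.

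**Conclusion.** The point holds for the strategy comparison only. The abstract misstates the allocation, and the exploratory MVC-versus-conference contrast has one randomised unit per strategy. Differences in effect or trend between the district groups cannot be told apart from strategy at any sample size, and the protocol names only power. The aliasing follows directly from the Trial design section and needs no assumption. Its practical size is unknown: the rejection rates of 12%, 32% and 50% at the planned sample depend on assumed gaps of 5, 10 and 13 points, a normal approximation, and a comparison of two independent stepped wedge effects. The two strategy-versus-control estimates and the sample size are untouched. This should be corrected, but it does not threaten the primary objective.

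**What to change.** - **Abstract:** say that two groups of six districts were derived from a cluster analysis (one after trimming for proximity), that strategy was assigned to the groups by one random draw, and that start year was randomised by district within group.
- **Objectives {7}:** state that MVC versus conference is a non-randomised contrast aliased with district group, in addition to being underpowered.
- **Analysis and reporting:** present the two within-group effects side by side, descriptively, with no hypothesis test and no claim that one strategy is superior. Label any interval for the difference as non-randomised.

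Adding district covariates is not a substitute: group itself cannot be adjusted for, and twelve districts leave little room to model the characteristics behind it.

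The cost is a few sentences and one exploratory inference given up. No new data are needed, and both primary analyses stay as they are.
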